# GLOSSARY OF STUDY-SPECIFIC TERMS

##### 5FC 5-fluorocytosine

ampho B amphotericin B deoxycholate (in A5225/HiFLAC, the abbreviated name is being used for convenience and is not intended to represent an official name for the drug)

ampho B-based regimen in this study, a regimen that is either ampho B alone or ampho B in combination with 5-fluorocytosine **or fluconazole, according to local standard of care**

CCTG California Collaborative Treatment Group

CM cryptococcal meningitis

CNS central nervous system

CSF cerebrospinal fluid

DLT dose-limiting toxicity: interruption of an induction dose of study-provided fluconazole (i.e., 1200 mg, 1600 mg, or 2000 mg daily) for at least 3 consecutive days as the result of a fluconazole-related toxicity, where the discontinuation was initiated prior to day 14

ECG electrocardiogram

EFV efavirenz

hERG human ether-a-go-go-related gene

HiFLAC High-Dose Fluconazole for Treatment in AIDS-Associated Cryptococcal Meningitis, acronym for A5225

IRIS immune reconstitution inflammatory syndrome

LFCrAg lateral flow cryptococcal antigen (assay)

LP lumbar puncture

MOPS manual of operations

MTD maximum tolerated dose, defined for A5225/HiFLAC as the highest dose of fluconazole that can be safely used [i.e., a dose that results in a ≤ 25% rate of fluconazole dose-limiting toxicity (DLT)].

PML progressive multifocal leukoencephalitis

SIP site implementation plan

SMC study monitoring committee

SoC standard of care

SoE schedule of events (protocol section 6.1)

TEN toxic epidermal necrolysis

TLT treatment-limiting toxicity: a toxicity that results in discontinuation of ampho B-based treatment prior to day 14 and prior to receipt of a total of 8.4 mg/kg ampho B

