## 7.0 CLINICAL MANAGEMENT ISSUES

A5225/HiFLAC sites must follow the DAIDS Table for Grading the Severity of Adult and Pediatric Adverse Events Version 1.0, December 2004, which can be found on the DAIDS DAIDS RSC Web site: <http://rsc.tech-res.com/safetyandpharmacovigilance/>, for grading toxicities related to study treatment.

Toxicity management at non-US CRSs may require reliance on clinical symptoms, clinician judgment, and available laboratory markers, since alternatives to study-provided treatment may be very limited and baseline levels may be different from those in other settings. It is understood that treating physicians will provide whatever available treatment is considered best to protect patient safety and well-being; compliance with study requirements must not compromise such treatment.

This section provides guidelines for management of toxicities related to **study-provided** fluconazole. Management of toxicities thought to be related to ampho B will be according to local standard of care. Guidelines for use of ampho B and management of the most common toxicities associated with it are included in section 5 of the A5225/HiFLAC MOPS and may be consulted, at the discretion of the site investigator.

Participants who permanently discontinue either fluconazole or **any** ampho B**-based regimen** because of an AE should be followed closely until resolution of the AE can be documented.

In the subsections below, ‘interruption’ is used to mean a temporary discontinuation, while ‘discontinuation’ is used to mean a permanent discontinuation. If study-provided fluconazole is interrupted for longer than 3 consecutive days, it must be discontinued and the participant must immediately be treated according to local standard of care (SoC).

The A5225/HiFLAC core team must be notified via e-mail ([[contact]](mailto:[contact])) within 3 business days after premature discontinuation of fluconazole or ampho B in Step 1 or Step 2.

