### 7.1 General Toxicities

The management of most fluconazole-related toxicities is summarized in this first section. Management of specific toxicities is addressed in the subsections that follow.

Grades 1 and 2: No change in treatment.

Grade 3 or 4: For a Grade 3 toxicity definitely, probably, or possibly related to fluconazole or for any Grade 4 toxicity, fluconazole should be reduced to 400 mg/day (or 600 mg/day if taking RIF) in Step1 and to 200 mg/day in Step 3. The reduced dose should be administered until toxicity resolves to a Grade ≤ 2 at which time fluconazole may either be escalated [e.g., to 400 mg/day (or 600 mg/day if taking RIF), 800 mg/day, and beyond, up to the assigned dose] or be resumed immediately at the assigned dose, at the discretion of the site investigator.

If the same Grade 3 or 4 toxicity recurs, fluconazole should be interrupted again and the A5225/HiFLAC core team should be contacted ([[contact]](mailto:[contact])).

For a Grade 3 toxicity not related or probably not related to fluconazole, no interruption is necessary.

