9.2.3 Exploratory Outcomes (to be described in separate analysis plans)

9.2.3.1 Pharmacology (see section 10.0).

9.2.3.2. Antifungal drug susceptibility of cryptococcal isolates.

9.2.3.3 Ability of LFCrAg assay to detect cryptococcal antigen in stored urine, serum, plasma, and CSF.

### 9.3 Sample Size and Criteria for Stages 1 and 2

9.3.1 Stage 1

The team feels that standard dose (400 mg/day) fluconazole would have about 5% DLT as defined in this study. To avoid the toxicity and difficulty of administration of ampho B, the team feels that ≤25% DLT would be acceptable. In the international setting and in participants with HIV and AIDS, the team also has concluded that there likely will be up to a 15% very early mortality rate in any cohort due to CM and/or HIV, not to the dose of fluconazole. Including participants who received very little fluconazole in safety evaluations to determine dose escalation could bias the evaluation either to be too high (if early deaths without toxicity are considered to be DLTs) or too low (if early deaths without toxicity are included in the denominator of the DLT rate). Thus, for primary safety evaluations, very early deaths (prior to Day 4) will not be included in the decision rule whether they experienced a DLT prior to early death or not [French, 2002; Okongo, 1998; Hakim, 2000; van der Horst, 1997; Brouwer, 2004; Pappas, 2004; Bicanic, Meintjes, et al, 2008; and Milefchik, 2008]. Should more than 6 very early deaths be seen in a cohort, enrollment to the cohort will by paused while the team evaluates the events carefully in conjunction with the SMC to consider if there should be study modifications. Secondary evaluations prior to escalation will include all subjects in a failure-time analysis of DLT with early deaths censored if DLT did not occur prior to death.

The dose escalation rule to be used in Stage 1 is:

- 0-3 DLTs; escalate to the next higher dose.
- 4-9 DLTs; do not escalate. This is the MTD.
- > 9 DLTs; the prior dose is the MTD.

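### The DLT definition does not clearly count toxicity handled by dose reduction, and has no limb for fluconazole-related death, so the DLT rate behind the MTD rule can be too low

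*Protocol*

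**What the plan says.** - **Glossary, DLT.** A DLT is "interruption of an induction dose of study-provided fluconazole (i.e., 1200 mg, 1600 mg, or 2000 mg daily) for at least 3 consecutive days". The cause must be toxicity related to the drug, and the stop must begin before day 14. No limb refers to toxicity grade, dose reduction or death. The maximum tolerated dose (MTD) is tied to a DLT rate of at most 25%.
- **Section 9.3.1.** The rule uses the DLT count alone. With 0–3 the dose escalates, with 4–9 the current dose is the MTD, and with more than 9 the prior dose is the MTD. On deaths soon after entry it states: "very early deaths (prior to Day 4) will not be included in the decision rule whether they experienced a DLT prior to early death".
- **Section 7.0.** In the subsections that follow it, the word interruption "is used to mean a temporary discontinuation".
- **Section 7.1.** For Grade 3 toxicity at least possibly related to fluconazole, or "for any Grade 4 toxicity, fluconazole should be reduced to 400 mg/day" (a higher figure applies with rifampin). The next paragraph says: "If the same Grade 3 or 4 toxicity recurs, fluconazole should be interrupted again".
- **Section 8.1.** A fluconazole DLT is listed among the reasons for stopping study treatment.
- **Sections 9.3.2 and 9.5.2.** Stage 1 and Stage 2 data are combined, with an adjusted confidence interval for the DLT rate at each dose.

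**The concern.** A dose-finding trial needs a DLT definition that catches participants who could not stay on the assigned dose because of the drug. Here the general management path for serious toxicity is a reduction, and section 2.2 gives reasons why reduction may be preferable to stopping. If a reduction is not an interruption, a participant moved well below the assigned dose for a related Grade 4 event adds nothing to the numerator and counts as tolerant in the denominator. The more closely sites follow section 7.1, the fewer DLTs are recorded. The same holds for a fluconazole-related death with no 3-day interruption before it. The omission works in one direction only, towards a lower rate, a higher apparent MTD and a lower combined DLT estimate.

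**Working it through.** **Step 1: which reading is better supported?**

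*Reduction is not an interruption.* Section 7.0 equates interruption with a temporary stop. Section 7.3 treats dose reduction and interruption as alternatives. Sections 9.2.2.5 and 9.3.2 list dose modifications separately from treatment interruptions. Section 8.1 makes a DLT a reason to stop treatment, yet section 7.1 lets a reduced participant continue and return to the assigned dose. If a reduction were a DLT, those two sections would conflict.

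*Reduction is an interruption.* The Glossary attaches the word to an induction dose and names the three assigned doses, so a participant on a lower dose has arguably interrupted that dose. Section 7.1 speaks of interrupting again after what was only a reduction. The meaning in section 7.0 is limited to the subsections of section 7.

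The first reading has more support, but the text does not settle it.

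**Step 2: reproduce the plan's figures.** Let n be the evaluable number and q the probability that a participant has a counted DLT. Then

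P(escalate) = Σ (k = 0 to 3) C(n,k) q^k (1−q)^(n−k).

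For n = 22 and q = .05, .10, .20, .30, .40, .50 this gives .978, .828, .332, .068, .008, .000. For n = 20 it gives .984, .867, .411, .107, .016, .001. All twelve escalation entries in Table 9-2 are reproduced.

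**Step 3: let a share go uncounted.** Let p be the true rate of related toxicity that keeps a participant off the assigned dose for at least 3 days, and f the share of it handled by reduction and not counted. The counted rate is q = p(1−f). The protocol gives no value for f, so 25%, 50% and 75% are assumptions.

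Worked case: n = 22, p = .30, f = .50, so q = .15. The terms for k = 0 to 3 are .028 + .109 + .201 + .237 = .575.

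| True p | f | Counted q | P(escalate), n = 20 | P(escalate), n = 22 |
|---|---|---|---|---|
| .30 | 0 | .300 | .107 | .068 |
| .30 | .25 | .225 | .310 | .237 |
| .30 | .50 | .150 | .648 | .575 |
| .30 | .75 | .075 | .942 | .922 |
| .40 | 0 | .400 | .016 | .008 |
| .40 | .25 | .300 | .107 | .068 |
| .40 | .50 | .200 | .411 | .332 |
| .40 | .75 | .100 | .867 | .828 |

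**Step 4: sensitivity to one case.** With 22 evaluable, 3 counted DLTs (3/22 = 13.6%) escalate and 4 (4/22 = 18.2%) do not. One participant classified differently can change the decision.

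**The case against.** The strongest case against is that several routes do bring serious toxicity into the count or before the decision makers.

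- Grade 3 QTc prolongation, Grade 3 rash and related Grade 3 or 4 hepatotoxicity lead to interruption, and Grade 4 QTc and rash to permanent discontinuation (sections 7.2, 7.3, 7.5). General toxicity that recurs is also to be interrupted. All of these can become DLTs. This stands, and it limits the gap to toxicity on the general path of section 7.1.
- The core safety team decides what is a DLT, events without unanimity count provisionally, and the monitoring committee reviews each cohort before escalation (section 9.4.1). Stage 2 dose choice considers grades and dose modifications (section 9.3.2), and section 1.3.3 looks at DLT and death combined. These make a poor decision less likely. They do not correct the DLT count or its interval, and the team has no written criterion for reductions or related deaths.
- Section 7.1 allows a return to the assigned dose once toxicity falls to Grade 2 or below, so short reductions would not count on any sensible definition. This stands. It is why p in the working covers only toxicity lasting at least 3 days off the assigned dose.
- The 5% and 25% benchmarks were set for DLT as the protocol now defines it, and section 5.1 describes Stage 1 as completed. Replacing the definition now would alter a primary safety measure after the data are known. This stands and shapes the fix.

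A reader might infer that fatal toxicity is excluded from the rule. The text does not say so: for related deaths from Day 4 onward it is silent. A reader might also make much of the exclusion of deaths before Day 4. A 3-day interruption can hardly be completed by then, and section 9.3.1 keeps any such DLT in a secondary failure-time analysis before escalation. That clause matters little in practice.

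**Conclusion.** The definition is ambiguous on dose reduction. On the better-supported reading it omits related toxicity handled by 3 or more days at a reduced dose. It has no limb for fluconazole-related death. Both gaps can bias the DLT rate low, in the MTD rule and in the combined Stage 1 and 2 interval.

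The possible effect is large, but its actual size is unknown. At n = 22 and 30% true toxicity, the chance of escalating rises from .068 to .237, .575 or .922 as the uncounted share goes to 25%, 50% or 75%. At 40% it rises from .008 to .068, .332 or .828. These figures assume independent participants and a share that the protocol does not give.

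A reader might conclude that toxicity met by a dose cut can never reach the rule, or that the MTD found in Stage 1 is wrong. Neither follows. A rival reading of the Glossary exists, named organ toxicities are interrupted, and nothing in the protocol shows how many participants were reduced instead of interrupted.

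**What to change.** 1. Reconcile the wording on interruption, reduction and DLT in the Glossary and sections 7.0, 7.1 and 8.1. Clinical management should not change through this edit. Because section 8.1 uses DLT as a stopping reason, it must say which meaning applies there, and the clinical team must settle that.
2. For counting only, state that a DLT is fluconazole-related toxicity starting before day 14 that keeps the participant off the assigned induction dose for at least 3 consecutive days, by interruption or reduction, or a fluconazole-related death.
3. Report the Stage 1 and the combined Stage 1 and 2 DLT rates under both the current and the expanded definition. The 25% limit and the cut-offs belong to the current one, so the expanded rate should sit beside it and not replace it. Keep the participant exclusions of section 9.1 in both.
4. Minor: in section 9.3.1, keep in the count any participant with a DLT or a fluconazole-related death before Day 4. This will rarely occur.

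The cost is a wording change and a re-read of dose modifications that section 6.3.7 already requires to be recorded and keyed. The downside is a DLT rate that may be reported as higher, with two figures to explain.

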# SCHEMA

A5225/HiFLAC

A Phase I/II Dose-Finding Study of High-Dose Fluconazole Treatment in AIDS-Associated Cryptococcal Meningitis

DESIGN Overview

A5225/HiFLAC is a phase I/II dose escalation and validation study of the safety, tolerability, and therapeutic effect of an induction-consolidation strategy of high-dose fluconazole alone **or with oral flucytosine (5FC)** for the treatment of cryptococcal meningitis (CM) in HIV-infected participants. As noted in section 2.2, comparison of this study’s results with historical data may be problematic. For this reason, a cohort treated with amphotericin B deoxycholate (which will be referred to as ‘ampho B’ in this study) alone or in combination with 5-fluorocytosine **or fluconazole, according to local standard of care** (**any** of which will be referred to as ‘an ampho B-based regimen’ in this document) will be included in this study.

The study will proceed in two stages (see A5225/HiFLAC Stages 1 & 2 Flow Chart). In Stage 1, Dose Escalation, up to three induction doses of fluconazole **alone** will be tested in sequentially enrolled cohorts. Stage 2, Dose Validation, will not open until the maximum tolerated dose (MTD) of fluconazole has been identified in Stage 1. In Stage 2, induction doses of fluconazole that are found to be safe in Stage 1 will be tested in simultaneously enrolled cohorts. In each stage, participants will be randomized at entry into Step 1. Over the course of the study, participants will register to subsequent steps (Steps 2-4) based on their initial randomization and/or their response to treatment. The study steps are:

- Step 1: Induction therapy with either high dose fluconazole or ampho B
- Step 2: Induction following early ampho B intolerance (only for participants randomized to ampho B treatment in Step 1) (fluconazole at 400-800 mg daily)
- Step 3: Consolidation therapy (fluconazole 400 mg daily)
- Step 4: Maintenance therapy (fluconazole 200 mg daily)

Stage 1 (Dose Escalation)

Stage 1 will include up to three sequentially enrolled cohort sets, each testing a different induction dose of fluconazole and gathering data about ampho B-based treatment (see A5225/HiFLAC Stage 1 Flow Charts #1-3). Each cohort will enroll up to 24 participants randomized to fluconazole and up to 8 participants randomized to an ampho B-based regimen. At any time during the study, enrollment may be halted for safety reasons.

- Cohort Set 1: fluconazole 1200 mg daily or ampho B-based regimen. Once the safety data for the last participant enrolled in Cohort 1 has been reported, reviewed, and found to be acceptable, Cohort 2 may be opened. Cohort 1 was opened to accrual on **x/x/x, and closed to accrual on x/x/2011**.
- Cohort Set 2: fluconazole 1600 mg daily or ampho B-based regimen. Once the safety data for the last participant enrolled in Cohort 2 has been reported, reviewed, and found to be acceptable, Cohort 3 may be opened. **Cohort 2 was opened to accrual on 10/7/2011 and closed to accrual on 6/x/2012.**
- Cohort Set 3: fluconazole 2000 mg daily or ampho B-based regimen. **Cohort 3 was opened to accrual on 7/x/2012 and closed to accrual on 8/x/2013.**

Fluconazole

Participants randomized to receive fluconazole will enter Step 1 and receive the assigned induction dose, adjusted for weight, for a minimum of 4 weeks and a maximum of 10 weeks.

In addition to the cerebrospinal fluid (CSF) samples collected at screening or entry, CSF samples will be collected at week 2 and every 2 weeks through week 10 until a negative culture is obtained. If a negative culture is obtained prior to week 10 (i.e., negative culture results are available at or before week 8 from a sample collected at least 2 weeks previously), the participant will enter Step 3 and will receive fluconazole 400 mg daily [or 600 mg daily if receiving rifampin (RIF)] until week 10. It is possible that a participant will not enter Step 3.

At week 10, all participants will enter Step 4 and receive fluconazole 200 mg daily through week 24. Note that participants randomized to fluconazole will not enter Step 2, which is described below.

Ampho B

Participants randomized to receive an ampho B-based regimen in Step 1 will receive amphotericin B deoxycholate at a dose of 0.7-1.0 mg/kg daily as part of the local standard of care (SoC) for approximately 2 weeks. At each site, the daily ampho B dose will be the same for each cohort.

In addition to the CSF samples collected for culture at screening or entry, CSF samples will be collected for culture at week 2 and again every 2 weeks through week 10 until a negative culture is obtained.

Participants who experience a treatment limiting toxicity (TLT), defined as a toxicity to ampho B treatment that results in discontinuation of that treatment prior to day 14 and prior to receipt of a total of 8.4 mg/kg ampho B, may either remain in Step 1 and receive an alternative treatment, such as liposomal ampho B, if available, or may enter Step 2 and receive study-provided fluconazole 800 mg or the maximum locally approved daily dose.

Participants who complete Step 1 will enter Step 3 after approximately 2 weeks.

For participants in Step 2, if negative CSF culture results are obtained prior to week 10 (i.e., negative culture results are available at or before week 8 from a sample collected at least 2 weeks previously), the participant will enter Step 3 and will receive fluconazole 400 mg daily (or 600 mg daily if receiving RIF) until week 10. It is possible that participants in Step 2 will not enter Step 3.

At week 10, all participants will enter Step 4 and receive fluconazole 200 mg daily through week 24.

Stage 2 (Dose Validation)

In Stage 1, when either the MTD of fluconazole is reached or the week 10 visit for the final participant randomized to the 2000 mg/day cohort is completed, all data through week 10 on all participants will be reviewed; the protocol will be amended before Stage 2 (Dose Validation) of the study opens. In Stage 2, participants will be randomized to receive an induction treatment of either an ampho B-based regimen or one of several doses of fluconazole **or fluconazole plus 5FC** at or below the MTD identified in Stage 1 (see A5225/HiFLAC Stage 2 Flow Chart).

Stage 1 and Stage 2 Evaluations

Participants will be monitored for safety and toxicity throughout the study period.

The primary efficacy outcome measure is the change in quantitative CSF culture for Cryptococcus at week 2. At screening or entry and again at week 2, CSF samples for culture will be collected from all participants. Additional CSF samples will be collected and cultured from participants on study treatment at weeks 4, 6, 8, and 10, as necessary until a negative culture is obtained. Treatment failure for any participant is defined as a positive culture from a CSF sample collected at week 10 and that is read by or at week 12.

Pharmacokinetic (PK) samples will be obtained at specified time points from all participants enrolled in fluconazole induction cohorts (see section 10.0 for sampling information).

DURATION 24 weeks

SAMPLE SIZE Up to 192 participants (up to 96 in Stage 1 and up to 96 in Stage 2).

POPULATION HIV-infected males and females ≥16 years of age presenting with their first episode of CM.

REGIMEN

Table 1: Stage 1 Regimens

| Cohort | N | Induction Step (Step1)  Daily Dose | Induction Following Ampho B Intolerance Step  (Step 2) | Consolidation Step (Step 3)  Daily Fluconazole Dose | Maintenance Step (Step 4) Daily  Fluconazole Dose |
| --- | --- | --- | --- | --- | --- |
| 1A1 | 24 | Fluconazole  1200 mg | N/A | 400 mg  Or 600 mg with RIF | 200 mg |
| 1B1 | 8 | Ampho B-based regimen;  0.7-1.0 mg/kg ampho B | Fluconazole  400-800 mg daily | 400 mg  Or 600 mg with RIF | 200 mg |
| 2A | 24 | Fluconazole  1600 mg | N/A | 400 mg  Or 600 mg with RIF | 200 mg |
| 2B | 8 | Ampho B-based regimen;  0.7-1.0 mg/kg ampho B | Fluconazole  800 mg daily or maximum locally approved dose | 400 mg  Or 600 mg with RIF | 200 mg |
| 3A | 24 | Fluconazole  2000 mg | N/A | 400 mg  Or 600 mg with RIF | 200 mg |
| 3B | 8 | Ampho B-based regimen;  0.7-1.0 mg/kg ampho B | Fluconazole  800 mg daily or maximum locally approved dose | 400 mg  Or 600 mg with RIF | 200 mg |

1 Enrollment to **Stage 1 ended on x/x/2013**.

Fluconazole dose adjustments based on weight must be implemented at the first dose; after entry, fluconazole dose adjustments in response to toxicities should be implemented on a case-by-case basis (see section 7.4).

Table 2: Stage 2 Regimens

| Cohort | N | Induction Step (Step1)  Daily Dose | Induction Following Ampho B Intolerance Step (Step 2)  Daily Dose | Consolidation Step (Step 3)  Daily Fluconazole Dose | Maintenance Step (Step 4) Daily  Fluconazole Dose |
| --- | --- | --- | --- | --- | --- |
| 4 | 24 | Ampho B-based regimen;  0.7-1.0 mg/kg ampho B | Fluconazole 800 mg daily or maximum locally approved dose | 400 mg  Or 600 mg with RIF | 200 mg |
| 5 | 24 | Fluconazole **1600 mg** | N/A | 400 mg  Or 600 mg with RIF | 200 mg |
| 6 | 24 | Fluconazole **2000 mg** | N/A | 400 mg  Or 600 mg with RIF | 200 mg |
| 7 | 24 | Fluconazole **2000 mg plus Flucytosine xx mg** | N/A | 400 mg  Or 600 mg with RIF | 200 mg |

Fluconazole dose adjustments based on weight must be implemented at the first dose; after entry, fluconazole dose adjustments in response to toxicities should be implemented on a case-by-case basis (see section 7.4). **Note that these dose adjustments are recommended only for study-provided fluconazole.**

A5225 Stages 1 and 2 Overview

Flow Chart

Study opens (Stage 1)

Cohorts 1A and 1B open; 32 participants are randomized 3:1 to an induction step of either fluconazole (at 1200 mg/day) or ampho B-based regimen.

